## Abstract

**Background:**

While surgical resection remains the primary treatment approach for symptomatic or growing meningiomas, radiotherapy represents an auspicious alternative in patients with meningiomas not safely amenable to surgery. Biopsies are often omitted in light of potential postoperative neurological deficits, resulting in a lack of histological grading and (molecular) risk stratification. In this prospective explorative biomarker study, extracellular vesicles in the bloodstream will be investigated in patients with macroscopic meningiomas to identify a biomarker for molecular risk stratification and disease monitoring.

**Methods:**

In total, 60 patients with meningiomas and an indication of radiotherapy (RT) and macroscopic tumor on the planning MRI will be enrolled. Blood samples will be obtained before the start, during, and after radiotherapy, as well as during clinical follow-up every 6 months. Extracellular vesicles will be isolated from the blood samples, quantified and correlated with the clinical treatment response or progression. Further, nanopore sequencing-based DNA methylation profiles of plasma EV-DNA will be generated for methylation-based meningioma classification.

**Discussion:**

This study will explore the dynamic of plasma EVs in meningioma patients under/after radiotherapy, with the objective of identifying potential biomarkers of (early) tumor progression. DNA methylation profiling of plasma EVs in meningioma patients may enable molecular risk stratification, facilitating a molecularly-guided target volume delineation and adjusted dose prescription during RT treatment planning.

## Background

Meningiomas comprise a family of neoplasms derived from meningothelial cells of the arachnoid mater, representing the most common primary intracranial tumor in adults [1]. Conventional histology-based WHO classification allotted 3 different grades to meningiomas for risk stratification - with increasing malignancy and risk of recurrence, ranging from WHO grade 1 to 3 ^1^. Meningioma cells were reported to secrete extracellular vesicles (EVs) (e.g. exosomes, microvesicles and oncosomes) into the bloodstream, which can be isolated for liquid biopsy [2–4]. A recent study by Ricklefs et al. investigated the dynamic of plasma EVs in meningioma patients following surgical resection. At initial diagnosis, meningioma patients displayed elevated levels of circulating EVs, as compared to healthy individuals. While preoperative plasma EV counts were positively correlated with WHO grading, decline of plasma EVs was reported to be associated with the extent of resection following surgical resection. Notably, plasma EV levels were not directly associated with tumor size, but correlated with the extent of tumor edema, indicating that leakiness of the blood-brain barrier may be responsible for the elevated levels of circulating EVs. Subsequent molecular classification revealed that DNA methylation profiling of EV-DNA may allow accurate allocation of patients into methylation subclasses, facilitating molecular risk stratification [2].

While surgical resection remains the primary treatment approach for symptomatic or growing meningiomas, fractionated external beam radiotherapy (RT) represents an auspicious alternative treatment approach in patients with meningiomas not safely amenable to surgery. Here, biopsies are often omitted in light of potential iatrogenic neurological deficits, resulting in an absence of histological grading and (molecular) risk stratification [1, 5, 6].

The present study aims to investigate the dynamic of plasma EVs in meningioma patients during radiotherapy and subsequent follow-up, which may serve as biomarker in treatment response and disease monitoring (e.g. early detection of relapse). Further, DNA methylation profiling of enriched plasma EVs may facilitate molecular risk stratification in meningioma patients, allowing a molecularly-guided target volume delineation and adjusted dose prescription during RT treatment planning.

## Methods/design

The study will be performed as a prospective, multicenter, explorative biomarker study. A total of 60 patients are projected to be enrolled into the study. Patients fulfilling the inclusion criteria will be treated with either photon- (intensity-modulated or 3D-conformal) or particle radiotherapy. The overall duration of the trial is scheduled to be 36 months, consisting of 24 months of recruitment and a minimum follow-up of 6 months. A flow chart for trial subjects is shown in Fig. 1.

**Fig. 1 Fig1:**
[figure not shown]
Study illustration

### Inclusion criteria

Inclusion criteria are defined as: macroscopic tumor in MRI (either as definitive RT, or following subtotal resection or relapse), confirmed meningioma (histologically or MRI/DOTATOC-PET CT), indication for radiotherapy, completed wound healing after surgical intervention, Karnofsky Performance Score ≥ 60%; age ≥ 18 years, written informed consent, ability of subject to understand character and individual consequences of the trial, and adequate contraception for women of childbearing potential.

### Exclusion criteria

Exclusion criteria are defined as: previous or known tumor diseases < 5 years ago, previous (cerebral) radiotherapy, simultaneous chemo/immunotherapy, evidence that the patient cannot adhere to the study protocol (e.g., non-compliance), the refusal of patients to participate in the study and participation in another clinical study or observation period in a competing trial.

### Radiation therapy

Radiation treatment will be carried out according to the current standard of care, following current clinical guidelines for meningiomas [6]. Target volume definition, the selection of treatment modality, total dose and fractionation are not study-specific. Simultaneous systemic therapies, particularly chemo- or immunotherapy, are not allowed in the current study. Patients will be immobilized with an individual immobilization mask for treatment planning.

All patients will receive a non-contrast planning CT scan (with a layer thickness of 3 mm) and a magnetic resonance imaging (MRI) for an optimal definition of the target volume. Dose constraints for normal tissues and organs will be respected according to the Quantitative Analyses of Normal Tissue Effects in the Clinic (QUANTEC) [7, 8]. According to the standard of care, intensity-modulated (photon) radiotherapy (IMRT) will be performed 5 fractions per week under image guidance with daily CT images and position correction using volumetric modulated arc therapy. If indicated, particle therapy will be carried out 5–6 fractions per week with protons or carbon ions, using active raster scanning for orthogonal X-ray image guidance and daily position correction. The target volume and the dose prescription will be defined at discretion of the treating radiation oncologist, following current clinical guidelines for meningiomas [6].

### Study visits

Clinical follow-up will be performed to clinical guidelines [6] and will not be study-specific, with exception of the collection of blood samples (EDTA). Patients will be followed-up for at least 6 months after radiotherapy, and thereafter every 6 months. Treatment response and progression will be defined according to the current guidelines established by the RANO working group [9].

Blood samples (EDTA) will be collected before start of radiotherapy, after application of approx. 50% of the total dose, after completion of radiotherapy and during clinical follow-up every 3–6 months until 2 years following radiotherapy. At each timepoint, 3 EDTA blood tubes à 7 ml will be withdrawn. The study visit plan is shown in Fig. 2.

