### Study endpoints

The primary aim of this study is to analyze the reduction of plasma EVs in meningioma patients following radiotherapy, as compared to the baseline prior to radiotherapy. This study is planned as an exploratory trial and therefore no formal sample size calculation was performed. Based on Ricklefs et al. [2], we assume a mean of 1.643 for the change in EVs with a standard deviation of 3.750. With 48 patients having values after 2 years (60 patients included with 20% drop-outs assumed), this results in a 95% confidence interval of width 2.178 [0.554; 2.732]. Descriptive statistics regarding changes at different time points including calculation of 95% confidence intervals. Changes over time will be graphically visualized. All patients with data available will be considered.

Secondary endpoints will be evaluated in all patients. Descriptive analysis (including Kaplan-Meier estimates for PFS and OS) will be provided using adequate statistics and calculation of 95% confidence intervals. Reasons for missing values will be described and considered in the interpretation of results. During clinical follow-up, the quantity of plasma EVs will be correlated with treatment response or tumor progression on MRI according to RANO guidelines, to address a potential correlation between level of plasma EVs and (early) tumor progression [9]. Further, methylation profiles of plasma EV-DNA will be generated for further molecular risk stratification into existing methylation families in meningioma [5]. If available (e.g. following resection or biopsy), further comparison, with the methylation family of the meningioma will be performed to validate the methylation classification of plasma EV-DNA.

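### EV levels are related to imaging only through RANO response or progression; if most patients stay in one category, information on tumour change is lost, so a continuous measure should be reported alongside

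*Protocol article*

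**What the plan says.** Three places in the protocol article describe the link between EVs and imaging, and all use the same scale.

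- Abstract, Methods: EVs will be "quantified and correlated with the clinical treatment response or progression".
- Study visits: "Treatment response and progression will be defined according to the current guidelines established by the RANO working group".
- Study endpoints: "the quantity of plasma EVs will be correlated with treatment response or tumor progression on MRI according to RANO guidelines", with the purpose "to address a potential correlation between level of plasma EVs and (early) tumor progression".

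No diameter, volume, percentage change or oedema measure is named as a correlate. PFS is also described by Kaplan-Meier, which again rests on progression as an event.

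The observation window is set by "24 months of recruitment and a minimum follow-up of 6 months" (Methods/design) and, in Study visits, by "Patients will be followed-up for at least 6 months after radiotherapy, and thereafter every 6 months". Blood is drawn "during clinical follow-up every 3–6 months until 2 years following radiotherapy". The cohort is 60 patients, with 48 assumed to have values at 2 years after 20% drop-out. All have macroscopic tumour on MRI at entry and an MRI for treatment planning.

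**The concern.** A RANO call is a category reached when tumour measurements cross a threshold, so all change short of the threshold is scored alike. Follow-up after radiotherapy may be as short as 6 months and EV sampling stops at 2 years. If few patients cross a threshold in that time, the outcome has little spread, the observed correlation is attenuated, and a handful of patients drive it.

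The analysis is formally secondary, but it serves a central aim. The Discussion describes the study's main purpose as finding out whether EV levels can be used to monitor disease after radiotherapy, and the Background mentions early detection of relapse. A threshold category is a coarse target for an early signal. At stake is the precision of the only EV–imaging association that the article names.

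**Working it through.** **Figures in the plan.** The article gives no figure for this correlation. Its only precision statement concerns the primary aim: mean change 1.643, SD 3.750, n = 60 × 0.8 = 48. The interval 1.643 ± t(0.975; 47) × 3.750/√48 gives [0.554; 2.732], width 2.178, exactly as printed. This confirms n = 48 as the plan's own evaluable number, which is used below together with n = 60.

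**Assumptions, not in the documents.** True correlation between EV change and tumour change 0.4; tumour change normally distributed; the shares in each RANO category as listed.

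**Step 1: information kept after cutting into categories.** For a standard normal variable cut at a and b, with shares p₁, p₂, p₃ and normal density φ, the share of variance kept under optimal scoring is

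E = φ(a)²/p₁ + [φ(b) − φ(a)]²/p₂ + φ(b)²/p₃.

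Example, 5/90/5%: φ(1.645) = 0.1031, so E = 2 × 0.1031²/0.05 = 0.425; the middle term is zero by symmetry. That is equivalent to 48 × 0.425 = 20.4 patients. The correlation becomes 0.4 × √0.425 = 0.261.

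**Step 2: approximate power, n = 48, two-sided 5%.** Power = Φ(atanh(r) × √45 − 1.96).

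- Continuous: Φ(0.424 × 6.708 − 1.96) = Φ(0.88) = 81%.
- 5/90/5%: Φ(0.267 × 6.708 − 1.96) = Φ(−0.17) = 43%.

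| Response/stable/progression (assumed) | Information kept | Equivalent n of 48 | Correlation | Power |
|---|---|---|---|---|
| Continuous measure | 1.000 | 48 | 0.400 | 81.1% |
| 0/95/5% | 0.224 | 10.7 | 0.189 | 25.0% |
| 5/90/5% | 0.425 | 20.4 | 0.261 | 43.3% |
| 10/85/5% | 0.527 | 25.3 | 0.290 | 51.8% |
| 10/80/10% | 0.616 | 29.6 | 0.314 | 58.7% |
| 20/70/10% | 0.715 | 34.3 | 0.338 | 65.6% |
| 25/60/15% | 0.778 | 37.4 | 0.353 | 69.6% |
| Equal thirds | 0.793 | 38.1 | 0.356 | 70.5% |

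**Step 3: simulation of the same model** (bivariate normal, Spearman, two-sided 5%, correlation 0.4). Ranges are across repeated runs.

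| | Continuous | 5/90/5% | 10/85/5% | 10/80/10% |
|---|---|---|---|---|
| n = 60 | about 87% | 48–50% | 58–59% | 66–67% |
| n = 48 | about 77% | 38–41% | about 48% | about 56% |

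The mean observed correlation falls from about 0.38 to 0.24–0.30. With a more generous 25% response and 10% progression, detection is about 75% (n = 60) and 65% (n = 48). At a true correlation of 0.3 with n = 60, it is 60% against 30–43%.

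**Step 4: number of events.** With 5% or 10% progressing, 48 × 0.05 = 2.4 or 48 × 0.10 = 4.8 progressions are expected.

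**Step 5: a model unfavourable to the concern.** Suppose true change is zero in stable patients, −60% in responders and +40% in progressors, with 8% measurement noise and cut-offs at −50% and +25% (all illustrative). With Spearman and n = 60, detection is 29%, 42% and 51% for the continuous measure against 74%, 80% and 79% for categories (shares 5/5, 10/5 and 10/10). With Pearson the two are about equal: 77–86% continuous against 81–85% categorical. Most of the reversal therefore comes from ranking pure noise among the stable patients.

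**The case against.** The strongest case against has five parts.

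- **The premise is not documented.** A reader might infer that meningioma changes so slowly that nearly everyone will be classed as stable. The article gives no growth rate, no response or progression rate and no RANO cut-offs, and it admits relapsed and subtotally resected tumours. This stands: the dominance of one category is a risk, not a fact. Nor does the article say that tumour measurements are recorded at every MRI.
- **The loss depends on the model.** If only responders and progressors truly change, categories lose almost nothing, and a rank correlation on the continuous measure does worse. This stands as a limit on the size of the loss and on the choice of method. Measurement error as such does not favour RANO, because the categories are cut from the same noisy measurements: with reliability 0.6, n = 48 and 5/5 shares, detection was 53% continuous against 25% categorical.
- **Prior evidence on size is weak.** The Background reports, from the cited surgical study, that EV levels had no direct relation to tumour size but did track oedema. That leaves the assumed correlation of 0.4 unsupported. It does not rule out a link with change in size after radiotherapy, and it is a reason to add oedema.
- **RANO matches the question.** Study endpoints and the Discussion ask about response and progression. A reader might conclude that percentage change should replace RANO; the documents do not support that.
- **The analysis is exploratory, and the article is condensed.** There is no test, alpha or power target to miss, and 95% confidence intervals are planned. The detection rates above only compare precision, so a claim that a null result would be uninterpretable goes too far. The full protocol or SAP may also name tumour measurements, so the point holds only as far as the article states.

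**Conclusion.** The concern holds in a conditional form. RANO response or progression is the only imaging correlate of EV quantity that the article names, and cutting a graded change into three categories loses information: about 21% even with equal thirds (1 − 0.793), and about 58% at 5/90/5% (1 − 0.425). With 5–10% in each extreme category and a true correlation of 0.4, detection drops from about 87% to 48–67% at n = 60 and from about 77% to 38–56% at n = 48. These figures rest on assumed shares, an assumed correlation and a normal model. If true change is confined to responders and progressors, the loss is small.

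This is a cheap improvement to a secondary, exploratory analysis. It is not a defect in the primary estimate of EV reduction, and it is not a reason to abandon RANO.

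**What to change.** In Study endpoints, keep RANO response or progression as the clinical read-out and add a co-reported analysis. At each visit with paired blood and MRI, estimate with a 95% confidence interval the association between within-patient EV change from the pre-radiotherapy sample and continuous percentage change in tumour measurement from the planning MRI. Add change in oedema extent as a second continuous correlate where it is recorded, given the evidence in the Background. Do not rely on a rank correlation alone, because it gives full weight to noise among patients whose tumours do not change; report a linear (Pearson or regression) estimate as well.

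Cost: entering the measurements in the study database and one more exploratory analysis. No additional patients, blood samples or study-specific scans are proposed. The drawback is measurement error in small changes, which keeping RANO alongside partly covers.

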**Fig. 2 Fig2:**
[figure not shown]
Study visits

### Study endpoints

The primary aim of this study is to analyze the reduction of plasma EVs in meningioma patients following radiotherapy, as compared to the baseline prior to radiotherapy. This study is planned as an exploratory trial and therefore no formal sample size calculation was performed. Based on Ricklefs et al. [2], we assume a mean of 1.643 for the change in EVs with a standard deviation of 3.750. With 48 patients having values after 2 years (60 patients included with 20% drop-outs assumed), this results in a 95% confidence interval of width 2.178 [0.554; 2.732]. Descriptive statistics regarding changes at different time points including calculation of 95% confidence intervals. Changes over time will be graphically visualized. All patients with data available will be considered.

Secondary endpoints will be evaluated in all patients. Descriptive analysis (including Kaplan-Meier estimates for PFS and OS) will be provided using adequate statistics and calculation of 95% confidence intervals. Reasons for missing values will be described and considered in the interpretation of results. During clinical follow-up, the quantity of plasma EVs will be correlated with treatment response or tumor progression on MRI according to RANO guidelines, to address a potential correlation between level of plasma EVs and (early) tumor progression [9]. Further, methylation profiles of plasma EV-DNA will be generated for further molecular risk stratification into existing methylation families in meningioma [5]. If available (e.g. following resection or biopsy), further comparison, with the methylation family of the meningioma will be performed to validate the methylation classification of plasma EV-DNA.

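### The precision stated for 2 years assumes 48 patients with values, but 24 months of recruitment within a 36-month study does not allow that number unless all 60 are treated in the first year

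*Protocol article*

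**What the plan says.** Three sections of the protocol article bear on the point.

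- **Study endpoints.** The primary aim is the change in plasma EVs after radiotherapy relative to baseline. No formal sample size calculation is made. In its place the section gives an expected precision: "we assume a mean of 1.643 for the change in EVs with a standard deviation of 3.750", and then "With 48 patients having values after 2 years (60 patients included with 20% drop-outs assumed", which leads to a 95% interval of width 2.178 [0.554; 2.732].
- **Methods/design.** "A total of 60 patients are projected to be enrolled into the study". The study is "scheduled to be 36 months, consisting of 24 months of recruitment and a minimum follow-up of 6 months".
- **Study visits.** Blood is taken before, during and after radiotherapy, and then "during clinical follow-up every 3–6 months until 2 years following radiotherapy". The guaranteed follow-up is shorter: "Patients will be followed-up for at least 6 months after radiotherapy, and thereafter every 6 months".

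**The concern.** The step from 60 to 48 removes drop-outs only. It makes no allowance for patients whose 2-year date falls after the study has ended. With recruitment over 24 of the 36 months, that loss is built into the calendar. It applies to everyone treated in the second recruitment year, however well they comply.

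The interval is the only quantitative support given for enrolling 60 patients, and it concerns the primary aim. A reader would take from it that the mean 2-year change will be known to within about ±1.09. If the calendar is as stated, the 2-year estimate will be clearly less precise.

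**Working it through.** **Inputs from the article.** 60 patients, 24 months of recruitment, 36 months overall (Methods/design). Last sample 2 years after radiotherapy (Study visits). Mean 1.643, SD 3.750, drop-out 20%, n = 48, width 2.178 (Study endpoints).

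**Assumptions, not in the article.** Even accrual, so 60/24 = 2.5 patients per month, and a radiotherapy course of R = 0 to 2 months. R = 0 also covers the case in which the 2 years are counted from enrolment.

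**1. Reproduce the stated interval.** Formula: mean ± t(0.975, n−1) × SD/√n. For n = 60 × 0.8 = 48, t(47) = 2.0117 and the half-width is 2.0117 × 3.750/√48 = 1.089. This gives width 2.178 and [0.554; 2.732], an exact match. The formula is right, so the question is whether n = 48 can be reached.

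**2. What 48 requires, whatever the accrual pattern.** A value 24 months after radiotherapy by month 36 needs radiotherapy to be finished by month 36 − 24 = 12. With 20% drop-out, 48/0.8 = 60, so all 60 must be enrolled and treated by month 12, halfway through recruitment. Even with no drop-out, 48/60 = 80% must be.

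**3. Two-year values under even accrual.** Patients who can reach the visit = 2.5 × (36 − 24 − R), then × 0.8.

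| Case | Reach 2 years | With values | Width | 95% interval |
|---|---|---|---|---|
| R = 0 | 30 | 24 | 3.167 | [0.060; 3.226] |
| R = 1.5 | 26.25 | 21 | 3.414 | [−0.064; 3.350] |
| R = 2 | 25 | 20 | 3.510 | [−0.112; 3.398] |
| R = 0, no drop-out | 30 | 30 | 2.801 | [0.243; 3.043] |

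Relative to the stated width: 3.167/2.178 = 1.45 and 3.510/2.178 = 1.61. The most favourable even-accrual case, with no drop-out and no time for radiotherapy, is still 2.801/2.178 = 1.29 times as wide.

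**4. Earlier visits on the same calendar.** Patients who can reach month v after radiotherapy = 2.5 × min(24, 36 − v − R), then × 0.8.

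- 6 months: 60 reach it and 48 have values, for R from 0 to 2. Width 2.178.
- 12 months: 60 (R = 0), 56.25 (R = 1.5) or 55 (R = 2) reach it, so 48, 45 or 44 have values. Width 2.178, 2.253 or 2.280 (for n = 44: 2 × 2.0167 × 3.750/√44).

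These widths hold only if SD 3.750 also applies at those visits.

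**5. Duration that would make 48 attainable at 2 years.** 24 (recruitment) + R + 24 = 48 to 50 months.

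**The case against.** The strongest reply is that the study is exploratory, disclaims a formal sample size calculation, and ties no test or success criterion to the interval. It describes changes at several time points in all patients with data, and no section names 2 years as the main one. This stands, and it limits the consequence. A reader might infer that the study is underpowered, or that a lower limit below zero defeats it. The article does not support that, because nothing is decided on whether the interval excludes zero. The reply does not rescue the figure, however. Analysing everyone with data does not create 2-year samples after the study has closed.

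Accrual could also be front-loaded, and the article gives no radiotherapy length. Both are fair, so 20 to 24 is a conditional figure and not a fixed yield. Step 2 of the working does not depend on either.

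Nor does the article show which statement is in error. A reader might infer that 36 months is right and 48 is wrong, but the duration may be the slip, since sampling to 2 years is planned for all patients.

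Two further stronger readings should be set aside:

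- **That the study ends at month 30, because 24 + 6 = 30.** The 6 months are a minimum and not an additive component. The article states 36 months, under which the last patient enrolled has 10 to 12 months after radiotherapy, in keeping with that minimum.
- **That 6 months should become the main time point.** That would change what is estimated. The Discussion raises a possible radiation-induced release of EVs into the blood, so an early value may not stand in for a late one. The assumed mean and SD come from a study of surgical resection, and nothing shows that they carry over to 6 months after radiotherapy.

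**Conclusion.** The point holds as an inconsistency between Methods/design, Study visits and Study endpoints. The interval is computed correctly for 48, but 48 two-year values do not fit the stated calendar unless every patient is enrolled and treated within the first 12 of the 24 recruitment months. With even accrual, 0 to 2 months of radiotherapy and 20% drop-out, about 20 to 24 values are available. The width is then about 3.2 to 3.5 instead of 2.178, and the lower limit lies between 0.060 and −0.112 instead of at 0.554. Front-loaded accrual would narrow the gap but would close it only in that extreme case. The precision promised at 2 years is wrong as written, while about the same precision is attainable at 6 and 12 months if the same SD holds.

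**What to change.** Reconcile the three sections in one of two ways.

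1. **Keep 36 months.** In Study endpoints, restate the 2-year number and width for that calendar (about 20 to 24 patients, width about 3.2 to 3.5) and state the accrual and radiotherapy-length assumptions. Add the precision at 6 months (about 48 patients) and 12 months (about 44 to 48), width about 2.2 to 2.3, noting that this takes the same SD. The cost is a less favourable 2-year figure, with no extra patients or visits.
2. **Keep 48 two-year values.** If 2-year values from all patients are intended, correct the overall duration in Methods/design to about 48 to 50 months. The cost is a study stated to be 12 to 14 months longer. The interval then stands as printed.

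The choice is the sponsor's. Either way, the loss of late-recruited patients at study end should be shown separately from drop-out.
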